#### Economic evaluation

We will conduct an economic evaluation alongside the three trials aiming to assess the cost effectiveness of Lina in comparison with usual lessons from a school perspective. The time horizon for the evaluation will be from the point of randomisation until the 6-month follow-up. Intention-to-treat analysis will be applied.

The primary outcome for our economic evaluation is the Quality Adjusted Life Years (QALYs), to be converted from the CHU-9D data by applying for the UK tariff [47]. Secondary outcomes include the EQ-5D-Y-3L and the Delaware Class Climate score. The outcomes data will be collected at baseline, post-intervention, and 6 months follow-up using the e-CRFs.

Resource use includes three groups, i.e. (1) time spent by teachers/psychologists on preparing and delivering *Lina* and usual sessions as well as other professionals’ time spent on delivering *Lina* and usual sessions, (2) resource use for providing necessary equipment to deliver Lina sessions and (3) time spent by teachers/psychologists and other professionals on providing additional support to students as well as managing students’ disruptive behaviours. We will collect relevant unit cost data to convert the quantity of resource use for each item to monetary values. The cost for resource use will be presented at student and time point level (i.e. baseline, immediately after intervention and 6 months follow-up). We will explore the appropriate approach to handle missing values in costs and outcome data. No discounting will be required for costs and outcomes data.

A cost-utility analysis will be performed on each country’s data to estimate the incremental costs of *Lina* compared to usual lessons per additional QALY gained (or the Incremental Cost-Effectiveness Ratio (ICER)). We will report the uncertainties around the point estimate of the ICER. Also, the point estimate will be compared against the country-specific willingness-to-pay threshold(s). We will pool data from the three countries together to conduct a multiple-country cost-utility analysis. A few sensitivity analyses will be performed including (1) using the EQ-5D-Y-3L and the Delaware Class Climate score as outcome measures (2) conducting economic evaluation under alternative scenarios related to implementation (e.g. frequency of session delivery) to help contextualise the findings for future implementation (3) applying for alternative approach(es) to handle missing values.

A Health Economic Analysis Plan will be signed off before the start of the economic evaluation.

#### Qualitative analysis plan

We will adopt a critical realist epistemological approach to analysing qualitative data. Focus group discussions and individual interviews will be digitally recorded (with consent) and transcribed verbatim in each country’s language. Transcripts will be anonymised before analysis. We will conduct reflexive thematic analysis using a phased coding approach in NVivo 12 Plus.

In phase 1, a select team of researchers across all trial sites (UK, Czechia and Portugal), and a gender champion (trained in qualitative coding techniques) will collaboratively develop a coding framework. Each team will conduct open coding on 3–5 initial transcripts per site to generate a coding framework, reviewing codes collaboratively for coherence, consensus and relevance to primary research questions. This framework will guide further exploration within specific areas of inquiry (i.e. will be used to constrain the data set to address specific research questions). Following the development of the coding framework, we will iteratively develop a multi-lingual comprehensive codebook via local language open and focused coding.

In phase 2, each country team will then code all qualitative data using the agreed framework with discrepancies reviewed collaboratively and new codes approved by the coordinating team for framework consistency.

Regular fortnightly meetings will be held to with the research teams and gender champion to incorporate multiple perspectives during both phases to strengthen the coding outcomes for coherence, consensus and relevance to primary research questions. Results will be structured into thematic categories that highlight how the evidence addresses the primary questions on Lina experiences and how these interact with vulnerability using reflexive thematic analysis.

#### Implementation evaluation analysis plan

The implementation evaluation will follow a mixed-methods design triangulating quantitative and qualitative data to assess feasibility, acceptability, appropriateness and fidelity of Lina delivery across countries.

Quantitative data on acceptability, feasibility and appropriateness from the teacher implementation measures will be analysed descriptively, reporting means, standard deviation and proportions of teachers a range of responses for each measure.

Fidelity will be assessed from structured observation forms, calculating the percentage of core Lina components delivered per session and comparing fidelity rates across countries using descriptive statistics. Teacher focus group discussions will be analysed using deductive thematic analysis with a priori codes derived from the primary research questions.

Quantitative teacher scores will be triangulated with qualitative themes from focus groups and structured observation data to examine alignment between teacher-rated implementation experiences and observed fidelity. Through this, we hope to identify contextual factors (barriers and facilitators) influencing implementation across the trial sites. Findings will be organised by country context to examine site-specific variations in implementation.

### Who will be included in each analysis {27b}

All randomised clusters (i.e. classroom) and their enrolled participants will be included in the primary analyses according to the intention-to-treat (ITT) principle, whereby participants will be analysed in the group to which their classroom was originally allocated (i.e. control or intervention).

### How missing data will be handled in the analysis {27c}

Analysis will follow the intention-to-treat principle, meaning all participants will be analysed in the groups to which their classes were assigned, regardless of protocol deviations where contamination may have occurred. Any protocol deviation will be reported to the Trial Manager and formally documented.

The proportion of missing data from each instrument in the trial assessments (i.e. student and teacher CRFs) will be summarised across assessment timepoints and their reasons will be described and discussed keeping in mind contextual realities within each trial site.

Missing data will be handled by multiple imputation by chained equations using the MI package in STATA and efforts will be made to ensure that imputed values stay within the valid range of each questionnaire. Results from the imputed dataset will then be combined using Rubin’s rules to produce final estimates that account for uncertainty due to missing data.

### Methods for additional analyses (e.g. subgroup analyses) {27d}

Additional and subgroup analyses will be fully detailed in the statistical analysis plan, including sensitivity analyses to examine the impact of missing data imputation.

Subgroup analyses will explore differential treatment effects across genders and across high (top quartile) versus not high (lower three quartiles) baseline levels of social anxiety (SAS-A).

The effect of adherence on sense of belonging (DCCS) will be examined via comparison of participants who received “sufficient” *Lina* to those that did not receive *Lina* or did not complete “sufficient” *Lina. *“Sufficient” *Lina* is defined as at least 4 *Lina* sessions, including the last 2 and either the first or second (based on the content of each session in the context of current knowledge on mechanisms of change).

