#### Secondary outcomes

In line with the developing *Lina* theory of change, secondary outcomes were selected to assess constructs anticipated to be affected by *Lina.* General wellbeing may be increased via increased belonging or other aspects associated with *Lina* such as exposure to the arts. Social anxiety and depression were selected as symptoms of mental distress that are both some of the most commonly experienced in adolescents, and (in the case of *social* anxiety) most likely to be positively impacted by *Lina*. Social awareness represents an area of psychological resources expected to be positively impacted by *Lina.* Loneliness is sometimes conceptualised as the counterpoint to belonging and is expected to be positively impacted by the positive class environment created by *Lina.* Finally, the *Lina* story touches directly on mental health issues in a way designed to reduce stigma. Measure selection was strongly influenced by availability of prior validation with young people in PT (where specific regulatory constraints exist around measures that can be used with young people in school settings), and by availability of data on sensitivity to change. Thus, the following student-report measures were selected. For all questionnaires, the total score (sum of all items) is the unit of analysis. For each outcome, the metric for analysis will be the mean difference in total or subscale scores between Lina and control groups at post-intervention, adjusted for baseline score and clustering via linear mixed methods models.WHO-5 Well-being Index is a 5-item measure of general well-being that has proven reliability and criterion validity among adolescents in the UK, Portugal and Czech Republic as part of a large cross-national validation study [19]. Scores are transformed to a score from 0 to 100, with lower scores indicating worse well-being [20].Patient Health Questionnaire-8 is an 8-item screening tool designed to assess the presence of depression symptoms [21]. PHQ-8 has strong equivalence with PHQ-9, has been tested for reliability and validity in 27 European countries—including the UK, Portugal and Czech Republic [22] and has demonstrated high internal consistency when administered with adolescents from vulnerable settings [23]. The total score can range from 0–24, with a score of ≥ 10 indicative of clinical-level depression [21].Social Anxiety Scale for Adolescents (SAS-A) is an 18-item questionnaire measuring adolescents’ social anxiety experiences in the context of peer relations [24] SAS-A has proven reliability and validity for Portuguese adolescents [25] and has been used in school-based screening of adolescents across France and Spain [26–28] with acceptable internal consistencies and validity. It contains three subscales: Fear of Negative Evaluation, Social Avoidance and Distress-New and Social Avoidance and Distress-General. Total score ranges from 0 to 90 with a higher score indicating a higher level of social anxiety [24].The 4-item University of California Los Angeles (UCLA) Loneliness Scale is a revised and shorter version of the full UCLA tool (20 items) [29]. The full UCLA scale demonstrated modest internal consistency in the assessment of loneliness in children and adolescents [30]. This version of the UCLA has been recommended by the Office of National Statistics in the UK [30, 31] as a strong measure of loneliness in youth aged 10–15 years, following adaptations. The tool has been translated and validated in Portugal and Slovakia with a modest internal consistency [32, 33].Social-Emotional Learning Edition of the Strengths and Difficulties Inventory System [brief version] (SSIS SELb) Social Awareness subscale is a 4-item assessment that evaluates the social-emotional skills of children and adolescents in relation to their social awareness. It measures how much students take into account others’ point of view, particularly those from different backgrounds [34]. SSIS SELb was translated and validated for use among school-going adolescents in 6 European countries including Portugal with a strong measurement for reliability and structural validity, supporting its use for international research with appropriate adaptation and translation [34].Peer Mental Health Stigmatisation Scale-Revised (PMHSS-R) Stigma Awareness subscale is 5-item assessment of individually held stigmatising beliefs. It is answered on a 5-point Likert scale of agreement [35]. PMHSS-R has been developed in Ireland [35] and validated in European contexts (Spain) [36] but there is no country-specific validation for the UK, Portugal and Czech Republic. However, at the time of drafting this protocol, PMHSS-R is currently the only validated tool that assesses both awareness and agreement of stigma and was considered justified in use for measuring these outcomes in the trial.EQ-5D-Y-3L is a child-friendly questionnaire to describe young peoples’ health across five dimensions: Mobility; Looking After Myself; Doing Usual Activities; Having Pain or Discomfort; and Feeling Worried, Sad or Unhappy [37]. Each dimension has three levels of response. The tool has been translated in Czech [38] and Portuguese [39] and demonstrates strong psychometric evidence for validity and reliability with adolescents in the UK [40] and among Portuguese speakers [39].Child Health Utility-9D (CHU-9D) is a self-report measure of health-related quality of life suitable for 7- to 17-year-olds. It consists of 9 dimensions each measuring a different domain (worried, sad, pain, tired, annoyed, schoolwork, sleep, daily routine and activities). Each domain has 5 levels of severity. The CHU-9D has been locally translated for administration among young people in Portugal, Czech Republic [41] and the UK and demonstrated modest internal consistency and validity among children, adolescents and young adults within the UK and Portuguese speakers [39].

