### Sample size {19}

#### Size of trial sample

Based on an assumed small to medium effect size (Cohen’s *d* = 0.4) based on school mental health meta-analyses [43], and a conservative Intraclass Correlation Coefficient (ICC) of 0.1 [44], which takes into account the clustering at the class and school level, and a design effect of 2.7, 40 classes per country will provide 90% power (alpha = 0.05).

The analysable trial sample assumes an average cluster size of 18 (a total of 720 participants per country). To allow for an anticipated drop-out rate of 20%, an average cluster size of 22 will be recruited at baseline (i.e. average 22 adolescents per classroom), thus giving a total sample size of 880 per country. The cluster size of 22 at baseline takes into account the variability in class sizes within and across each country, and expected number of participants who opt out of the study.

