## Statistical methods

### Statistical methods for primary and secondary outcomes {27a}

#### Statistical analysis

Data for the three trials will be analysed separately (by country), before later being pooled for overall analysis.

Participant level socio-demographic data and cluster level (classroom) data will be summarised at baseline for both arms of the trial.

The primary outcome is the Delaware Class Climate score at the end of *Lina* delivery (8–10 weeks post baseline and follow-up). This will be compared between *Lina* and control groups using a linear mixed effects model with a random effect for classroom and school, allowing for the clustering of children, within classes, and within schools. The model will include baseline level of the Delaware Class Climate as a covariate, as well as demographics (that are known to affect outcome). The analysis will use intention to treat by including all participants in the arm to which they were randomised, whether or not they completed the *Lina* programme and including all students in the analysis by using multiple imputation. We will set out in the statistical analysis plan (SAP) how missing data will be handled, including planned sensitivity analyses.

Secondary outcomes are WHO-5, PHQ-8, SAS-A, UCLA Loneliness Scale, SSIS SELb, PMHSS-R, EQ-5D-Y-3L and CHU-9D all measured at post-intervention (T1) and 6 months post baseline (T2). Each variable will be analysed using a generalised linear mixed effects model with a link function appropriate to the outcome distribution, with random effects for classroom and school. All models will include the baseline value of the outcome.

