### Protocol and statistical analysis plan {5}

A full statistical analysis plan (SAP) will be developed prior to exporting data from the database and reviewed by the trial steering committee. Data analysis will not be conducted prior to final sign off of the SAP. The SAP will be made publicly available prior to data lock. Once country level data has been analysed, then data from across the three countries will be pooled and analysed as one dataset. This will follow analysis as described above but with further level of clustering at the country level. The full analysis plan for the pooled analysis will also be described in the SAP. The trial statistical analysis plan (SAP) will be finalised before the database lock and published on University of Birmingham’s OSF record as well as to the study protocol as an update at a later stage. This study protocol will be made publicly accessible through publication in a peer-reviewed journal as well as the ISRCTN record (https://www.isrctn.com/ISRCTN11613092).

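### The social-anxiety subgroup test cuts baseline SAS-A at its top quartile, which loses about 36-46% of the information on a roughly linear interaction, and the reference sample for the quartile is not stated

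*Protocol article*

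**What the plan says.** The section on additional analyses {27d} names two subgroup questions: gender, and baseline social anxiety. The second is defined as a contrast "across high (top quartile) versus not high (lower three quartiles) baseline levels of social anxiety (SAS-A". No norm, clinical threshold or fixed score is given for the cut, so a sample quartile is the natural reading. No reason is given for using a threshold. The section leaves further detail to the SAP: "Additional and subgroup analyses will be fully detailed in the statistical analysis plan".

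Under Secondary outcomes, SAS-A is an 18-item questionnaire: "Total score ranges from 0 to 90 with a higher score indicating a higher level of social anxiety". That section makes the total score the unit of analysis for all questionnaires, and the participant timeline shows SAS-A collected at baseline.

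On countries, the Statistical analysis section says: "Data for the three trials will be analysed separately (by country), before later being pooled for overall analysis". Of the pooled analysis, the section on the protocol and SAP {5} says: "This will follow analysis as described above but with further level of clustering at the country level". Neither says how the SAS-A quartile is formed.

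**The concern.** Cutting a continuous modifier treats a student just below the cut like one far below it, and a student just above it like the most anxious student in the sample. When the treatment effect changes gradually with the modifier, that discards information the trial already holds. An interaction test is weak to begin with in a trial sized for a main effect, and the split weakens it further. A null result could then be read as evidence that *Lina* works equally well at all levels of social anxiety, when the test had little chance of showing otherwise. The question matters to the programme: the protocol states an interest in students vulnerable to poor mental health, and its rationale for the secondary outcomes singles out social anxiety as the kind of distress most likely to benefit.

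The contrast itself is written into the protocol, so a SAP that follows it inherits the split. The unstated reference sample is a smaller, separate gap. It determines who counts as high in each country analysis and in the pooled one.

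**Working it through.** **1. The plan's own power figure.** The sample-size section gives: "Based on an assumed small to medium effect size (Cohen’s *d* = 0.4"; "a conservative Intraclass Correlation Coefficient (ICC) of 0.1"; "a design effect of 2.7, 40 classes per country will provide 90% power (alpha = 0.05". It assumes 18 analysable students per class and 720 per country. Allocation is 1:1. A two-sided alpha is assumed, because sidedness is not stated.

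- Design effect = 1 + (18 − 1) × 0.1 = 2.7, as stated.
- Effective number per arm = 360 / 2.7 = 133.3.
- Power = Φ(0.4 / √(2/133.3) − 1.96) = Φ(3.266 − 1.96) = 90.4%, against 90% stated. A t reference with 38 degrees of freedom gives 88.9%.

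The figure reproduces. It covers the main comparison; no power is given for any interaction.

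**2. Size of the high group.** 720 × 0.25 = 180 students per country, about 90 per arm, or 180 / 40 = 4.5 per class.

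**3. Information kept by the split.** For a linear interaction, the share of information kept when a score X is replaced by its top-quartile indicator G is the squared correlation of X and G.

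- Normal score: φ(z at 0.75)² / (0.25 × 0.75) = 0.3178² / 0.1875 = 0.539. Loss 46%.
- Uniform score (variance 1/12): covariance = 0.25 × (0.875 − 0.5) = 0.09375; 0.09375² / (0.1875/12) = 0.5625. Loss 44%.
- Right-skewed gamma scores, by simulation with 2,000,000 draws: 0.606 kept at skewness 0.67, 0.628 at 1, 0.642 at 1.41, 0.640 at 2. Loss 36-39%.

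The documents do not give the distribution of baseline SAS-A, so the working range is a loss of about 36-46%. For this test, that amounts to keeping between 0.539 × 720 = 388 and 0.642 × 720 = 462 of the 720 students. A median split of a normal score would lose 36.3%.

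**4. What this does to power (illustration).** Assumptions that are not in the documents: residual variance 0.9 SD² (1 minus the ICC of 0.1), a normal score, and interaction slopes b in outcome SD per SD of SAS-A. The standard error of the continuous interaction is √(0.9 / (720 × 0.25)) = 0.0707. Power is Φ(b/0.0707 − 1.96) for the continuous test and Φ(b√0.5386/0.0707 − 1.96) for the split.

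| Assumed slope b | Continuous | Top-quartile split |
|---|---|---|
| 0.10 | 29% | 18% |
| 0.20 | 81% | 55% |
| 0.25 | 94% | 74% |
| 0.30 | 99% | 88% |

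**5. The reverse case.** The squared correlation is symmetric. If the true pattern is a step exactly at the quartile, the split keeps all the information and a linear term keeps 54% (normal score). The ranking of the two tests therefore depends on the shape of the effect, and the loss in step 3 applies only to a roughly linear one.

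**The case against.** The strongest defence is that the split matches the question as worded. The aim is to explore whether the most anxious quarter responds differently from the rest, and a two-group contrast answers that in a form schools can read. The rule is fixed in advance, which limits choosing a cut after seeing results. If the effect really is confined to highly anxious students, the split may be the better test. All of this is fair. It supports keeping the contrast as a display, but it does not make a strong case for using it as the only stated test, since the protocol gives no reason to expect a threshold at the upper quartile.

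A second defence is that the SAP, which is not shown, may add a continuous interaction or further subgroups. It may. The contrast is nevertheless stated in the protocol, and no continuous analysis of the modifier appears there.

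Two stronger readings are tempting and are not supported. A reader might infer that high will mean a different SAS-A score in each country, because the countries are analysed separately. If the quartile is formed within each trial, that is very likely. The protocol does not say so, and one common cut is not excluded; the supportable point is that the reference sample is unstated. A reader might also conclude that one set of fixed scores should define high in all three countries. That presumes scores carry the same meaning across languages. The Secondary outcomes section cites SAS-A validity for Portuguese adolescents and use in France and Spain, but nothing for Czech or UK students. A within-country position could be the safer definition.

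**Conclusion.** The point holds in a limited form. The protocol fixes an inefficient test for one of its two named subgroup questions. The loss is about 36-46% of the information on the interaction: 46% if baseline SAS-A is normal, less if it is right-skewed. This rests on a roughly linear interaction and an assumed distribution, neither of which the documents give. It would not be right to say without qualification that nearly half the information is discarded, because a threshold effect at the quartile would favour the split. The reference sample for the quartile is also undefined.

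The consequence is small. The analysis is exploratory, and the primary outcome, its model and the sample size are untouched. It is worth correcting because the correction is cheap and the SAP is due to be finalised before database lock.

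**What to change.** In the SAP, and in the subgroup paragraph if the protocol is next amended:

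- Make the interaction of arm with continuous baseline SAS-A (centred) the main social-anxiety subgroup test, in each country and in the pooled analysis, with a spline or other non-linearity check.
- Report the estimated *Lina* effect with confidence intervals at SAS-A values stated in advance.
- Keep the top-quartile contrast as a secondary display, and state beforehand whether the quartile is taken within country or over the pooled sample.

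The cost is wording; no new data are needed. The downside is that a linear term is less efficient if the true effect is a threshold. The non-linearity check and the retained quartile display cover that case.

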### Strategies to improve adherence to intervention/comparator {15c}

We will develop Standard Operating Procedures (SOPs) around consenting procedures, data collection and management and intervention delivery to ensure fidelity and adherence to the protocol. All implementation researchers will fill out session logs to introduce a standard monitoring framework for data quality.

Although we do not have any target tools to measure adherence and fidelity specifically, we will be monitoring fidelity and adherence to the intervention recording the number and content of each session using observation forms which will be filled out by researchers facilitating *Lina* lessons.

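### The adherence analysis is an as-treated contrast: it breaks randomisation and can show a benefit even if Lina does nothing

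*Protocol article*

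**What the plan says.** Section 27d (Methods for additional analyses) announces an adherence analysis of the belonging score: "The effect of adherence on sense of belonging (DCCS) will be examined via comparison of participants who received" 'sufficient' Lina, against participants who had no Lina or did not reach that level. 'Sufficient' means at least four sessions, which must include the last two and one of the first two. The section leaves further detail of additional analyses to the SAP, which is not available here, but it fixes the two groups and the threshold itself.

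The primary analysis is separate. Sections 27a, 27b and 27c all analyse students in the arm to which their class was allocated.

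Three other places bear on the point. The Background (9a) reports that a greater sense of school belonging goes with less truancy. Section 15b lists why sessions may be lost: individual students may be excused or stopped over safeguarding concerns, and whole classes may lose sessions through closures, strikes or staff shortages. The comparator description says that control classes receive Lina only in the next school year.

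**The concern.** The exposed group can contain only Lina-arm students, and only those who attended enough. Students of the kind who miss sessions leave the Lina side and join the comparator, while their counterparts in control classes were in the comparator already. The two groups therefore differ in the type of student as well as in exposure.

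Belonging is both the outcome and, by the protocol's own background, a correlate of attendance. If would-be adherers have higher belonging after whatever adjustment is made, the contrast is positive under a null effect. At stake is a supporting result described as an effect of adherence that could make a null trial look effective among students who attended.

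**Working it through.** **Planned effect and power, as the yardstick.** The sample size section gives d = 0.4, a "conservative Intraclass Correlation Coefficient (ICC) of 0.1", "a design effect of 2.7" and an "average cluster size of 18 (a total of 720 participants per country").

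- Design effect: 1 + (18 − 1) × 0.1 = 2.7.
- Effective n per arm: 360 / 2.7 = 133.3.
- Two-sided power at alpha 0.05: Φ(0.4 × √(133.3/2) − 1.96) = Φ(1.306) = 0.904.

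This agrees with the statement that "40 classes per country will provide 90% power". The protocol states no figure for the adherence analysis.

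**Bias of the contrast when Lina has no effect.** Let p be the share of Lina students with 'sufficient' Lina, and δ the difference in belonging (SD units, after any adjustment) between would-be adherers and non-adherers. Both are assumptions. Put both arm means at 0.

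- Adherers: δ(1 − p). Non-adherers: −δp.
- Comparator (a full control arm plus a share 1 − p of non-adherers): −δp(1 − p)/(2 − p).
- Difference: 2δ(1 − p)/(2 − p).

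Example: p = 0.8, δ = 0.5 gives 2 × 0.5 × 0.2 / 1.2 = 0.167.

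**The same contrast in a mixed model.** Simulation with 40 classes of 18, ICC 0.1, a class random effect only, no baseline covariate, 4,000 runs per setting and no Lina effect:

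| p | δ | Unweighted bias | Bias with class effect | False positives at two-sided 0.05 |
|---|---|---|---|---|
| 0.7 | 0.1 | +0.05 | +0.07 | 11% |
| 0.7 | 0.3 | +0.14 | +0.21 | 62% |
| 0.7 | 0.5 | +0.23 | +0.36 | 97% |
| 0.8 | 0.1 | +0.03 | +0.06 | 9% |
| 0.8 | 0.2 | +0.07 | +0.12 | 23% |
| 0.8 | 0.3 | +0.10 | +0.18 | 44% |
| 0.8 | 0.5 | +0.17 | +0.29 | 85% |
| 0.9 | 0.1 | +0.02 | +0.04 | 7% |
| 0.9 | 0.3 | +0.05 | +0.12 | 21% |
| 0.9 | 0.5 | +0.09 | +0.19 | 45% |

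At δ = 0 there is no bias and about 5% false positives. At δ = −0.2 and p = 0.8 the model-based bias is −0.12 SD, a false harm. The class effect enlarges the bias because the model leans on the comparison of adherers with non-adherers inside Lina classes, which under the null is pure selection.

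**Narrower reading.** If the comparator meant only non-adherent students in Lina classes, the null difference would be δ(1 − p) + δp = δ, the whole gap.

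**Allocation as instrument.** The estimator is the intention-to-treat difference divided by the share with 'sufficient' Lina.

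- Null settings: mean estimate between −0.004 and +0.003 SD; the intention-to-treat test rejects in 4.5% to 5.9% of runs.
- True effect 0.4 in adherers only, p = 0.8: it returns 0.32 / 0.8 = 0.40, whether δ is 0 or 0.3. The protocol's contrast returns 0.40 and 0.58.
- Partial Lina also worth 0.4, p = 0.8, δ = 0: it returns 0.40 / 0.8 = 0.50, too high, and the protocol's contrast returns 0.21, too low. In general, a partial effect τ adds τ(1 − p)/p, here 0.4 × 0.2 / 0.8 = 0.10.

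**The case against.** The strongest reply is that this is one additional analysis beside an intention-to-treat primary. The SAP, to be reviewed by an independent statistician and signed off before analysis, will set the model and covariates. Adjustment for baseline belonging could shrink δ. Lina runs in routine lessons for whole classes, and class-level losses select less by student. Much of this stands and limits the weight of the point. It does not remove it, because the protocol fixes the compared groups and no choice of covariates restores randomisation.

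A reader might infer that the contrast will necessarily favour Lina. The documents do not support that. The truancy association gives a direction but no size, and no attendance rate is stated. If partial Lina works, the contrast can understate the effect.

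A reader might also infer that attendance per student is not collected, since section 15c says that "we do not have any target tools to measure adherence and fidelity specifically" and describes "recording the number and content of each session using observation forms which will be filled out by researchers". But the same sentence goes on to commit to monitoring adherence, a researcher is present at every session, and the definition of 'sufficient' presupposes exposure known for each participant. How attendance is linked to participants is operational detail that a condensed article may omit.

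Finally, a complier-average effect is not free of assumptions. It treats less than 'sufficient' Lina as having no effect. That is doubtful for an intervention aimed at class climate, where a student who missed sessions may still gain through classmates.

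**Conclusion.** The point holds. The adherence comparison is as-treated, breaks randomisation and can show a benefit when Lina does nothing; the protocol's own background makes that the likely direction, not a certain one. With no Lina effect, 80% adherence and a residual gap of 0.1 to 0.5 SD, the bias is about +0.03 to +0.17 SD unweighted (8% to 42% of the planned 0.4) and about +0.06 to +0.29 SD with a class random effect. Adherence and gap are both assumed. The result is zero with no gap and negative with a reversed one. The primary analysis is not touched, so this is a change that should be made to a supporting analysis, not a threat to the main conclusion.

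**What to change.** In the SAP, replace the contrast with a complier-average causal effect. Use class allocation as the instrument for 'sufficient' Lina, with its definition unchanged, the baseline belonging score as covariate, standard errors clustered by class, and all randomised enrolled students included. Because control classes wait until the next school year, non-adherence should be almost entirely on the Lina side, which keeps the estimator simple.

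State the assumption that less than 'sufficient' Lina has no effect, and vary it in sensitivity analysis. One way is to lower the exposure threshold, for example to any session. Another is to assume a range of partial effects τ and subtract τ(1 − p)/p from the estimate.

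If the protocol's contrast is kept as well, label it observational and do not describe it as an effect of Lina.

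The cost is SAP wording, which can still change because the SAP is to be finalised before database lock. The downsides are a wider interval than the as-treated one (at 80% adherence roughly 1 / 0.8 = 1.25 times the width of the intention-to-treat interval) and dependence on the stated assumption.
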